### Acceptability

Acceptability of the intervention will be assessed using data acquired through the online SilverCloud system on usage and engagement with the intervention, including percentage of participants completing each module, average number of log ins, average time spent per session, and total time spent on the program.

We will also gather descriptive data on the feasibility of the recruitment process, such as numbers who expressed interest in participating, numbers who received links to the programs, and, of those, how many completed screening measures and how many used the program. Additionally, we will gather data on numbers recruited at each site and numbers of students selecting each of the three programs. These data will help to develop realistic estimates of enrollment accrual and attrition rates.

### Satisfaction with treatment

The satisfaction with treatment (SAT) questionnaire [40] includes nine quantitative questions regarding satisfaction with accessing treatment online (e.g., How did this online treatment compare to previous treatments? 0 = “much better” to 4 = “not at all good”). The satisfaction measure also contains two qualitative questions asking participants to describe what they most liked and least liked about the online treatment.

### Semi-structured interviews

Semi-structured interviews will include a schedule of questions derived from the literature that will explore the participants’ perceptions, attitudes, and experiences of the intervention. Interviews will be conducted by doctoral students via telephone and will last no more than 60 min.

### Ethical considerations

Information made available to all prospective participants will inform them of exactly what is involved in participating, including the objectives of the trial. Participants will know that their involvement is voluntary and they can withdraw their participation at any time without prejudice. Informed consent will be collected online via checking a box indicating that they consent to participate.

### Planned statistical analysis

Acceptability data in terms of usage and engagement will be assessed by analyzing the percentage of participants completing each module, the average number of logins, the average time spent per session, and total time spent on each of the three programs. As mentioned, feasibility will be assessed by analyzing the number of participants recruited at each site and the number of students selecting each of the three programs overall and at each site.

Satisfaction data will be analyzed using the descriptive and interpretative framework described by Elliott and Timulak [13].

Descriptive data will be presented from the semi-structured interviews. The transcriptions will be analyzed thematically using a pre-determined framework derived from the interview schedule and adapted and revised based on participant responses [45].

The outcome data will be treated as preliminary and interpreted with caution. Statistical analysis will be used to describe the characteristics of the sample and to provide initial estimates of parameters needed to inform the design of a future RCT. To assess whether change can be seen in the three programs, within group effect sizes (Cohen’s *d*) assessing change from baseline to 8 weeks and 3 months will be calculated. For Cohen’s *d*, an effect size of 0.2 to 0.3 can be considered a small effect, around 0.5 a medium effect, and 0.8 upwards a large effect [7]. A repeated measure ANOVA will be used to analyze the differences in the symptom outcomes across time points. An estimation of recovery will be made by identifying the number of participants completing each program who demonstrated a reduction of 50 % from pre-treatment PHQ-9, GAD-7, and DASS-21 stress subscale scores [39]. In addition, we will calculate the number of reliably changed and recovered participants using Jacobson and Truax’s [20] criteria.

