**Methods/design:**

The study is an open feasibility trial of the SilverCloud programs for depression (Space from Depression), anxiety (Space from Anxiety), and stress (Space from Stress). All three are 8-module internet-delivered CBT (iCBT) intervention programs. Participants are assigned a supporter who provides weekly feedback on progress and exercises. Participants will complete the Patient Health Questionnaire-9 (PHQ-9), Generalized Anxiety Disorder-7 (GAD-7), and stress subscale of the Depression, Anxiety, Stress Scale-21 (DASS-21) as the outcome measures for the depression, anxiety, and stress interventions, respectively. Other outcomes include measures of acceptability of, and satisfaction, with the intervention. Data will be collected at baseline, 8 weeks and 3-month follow-up.

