### Objectives of the trial

The aim of this study is to test the acceptability of internet-delivered treatment for depression, anxiety, and stress in university students. The trial will investigate the feasibility of recruiting students (in relation to numbers screened, numbers recruited, and level of adherence) to receive internet-delivered interventions for the treatment of depression, anxiety, and stress and establish the acceptability of the interventions to the students at University of Minnesota.

Acceptability of the intervention to clients will be assessed using data on usage and engagement with the intervention (e.g., percentage of participants completing each module, average number of logins, average time spent per session, and total time spent on the program). These data are acquired through the online SilverCloud system. Satisfaction will be assessed through the use of a post-intervention questionnaire on satisfaction with accessing and using an online delivery format for treatment. At 3 month-follow-up, all 105 participants will be contacted by email and invited to complete a semi-structured interview about their perceptions, attitudes, and experiences of the intervention. The first 25 to respond will be asked to complete the interview. The interview sample will include participants who dropped out of the intervention.

The trial also hopes to establish the potential for change and to establish initial estimates of the effectiveness of these online interventions for students in terms of within-group effect sizes associated with changes in depression, anxiety, and stress from baseline to 8 week and 3 months follow-ups. These data will be used to estimate the sample size for a future trial to ensure that the study is sufficiently powered. A conservative estimate using the 90 % upper confidence limit will be used to inform the sample size calculation of the future RCT.

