### Recruitment procedure

Participants will be recruited through three units at the University of Minnesota-Twin Cities, a public research university located in Minneapolis and St. Paul, Minnesota. The first unit is Student Counseling Services (SCS) which provides free short-term counseling to undergraduate and graduate students. The second is Boynton Mental Health Clinic (BMHC) which also provides short-term psychological services to full-time students at the University of Minnesota. Unlike SCS, BMHC also has psychiatrists on staff and is affiliated with the university health service. Finally, we will recruit participants through the International Student and Scholar Services (ISSS) office which provides counseling to foreign national students on campus.

The SilverCloud programs will be advertised to students through the three participating offices on campus via staff referrals, brochures, flyers, email announcements, and web sites and through the general student mental health web site. Regardless of how they learn about the programs, students can sign up online to get access to the programs. If a student expresses interest, they will be emailed a link to a web site with more information about the programs and the study. Interested students will sign the consent form and complete screening measures online and will be given feedback on their scores. This feedback consists of informing students of their overall score for each measure and whether their score indicates mild, moderate or severe depression, anxiety, or stress. This will allow them to make an informed decision on choosing one of the three programs. They will then be referred to a supporter from within the service where they learned about the study. Participants’ post outcome measures will be gathered 8 weeks after their initial log in or activation of the program and 3 months later (5 months after initial log in).

A second recruitment phase will be conducted at 3-month follow-up. All 105 participants will be contacted by email and invited to complete a semi-structured interview about their perceptions, attitudes, and experiences of the intervention. From those that respond expressing an interest, the first 25 will be selected to complete a semi-structured interview.

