### Sample size

A sample size of 35 participants per group is the standard expectation for feasibility studies [52]. This sample size will allow us to estimate the standard deviation of the symptom outcome measures (for the proposed RCT). We thus aim to recruit 105 participants in total across the three trial arms (see Fig. 1). In addition, a sample of between 10 and 15 people would be suitable to reach saturation through analysis of data collected in semi-structured interviews [16].

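### The planned repeated-measures ANOVA, in its classical form, drops 8-week scores of students who miss the later follow-up; a mixed model would use them at no extra cost

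*Protocol article*

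**What the plan says.** Under Planned statistical analysis, the protocol article fixes the method for the symptom scores: "A repeated measure ANOVA will be used to analyze the differences in the symptom outcomes across time points". The abstract gives the schedule: "Data will be collected at baseline, 8 weeks and 3-month follow-up". Recruitment procedure ties it to first use of the program: "post outcome measures will be gathered 8 weeks after their initial log in or activation of the program and 3 months later", so the last assessment falls about five months after log-in. Under Measures, every outcome is an online self-report.

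The target is set under Sample size: "A sample size of 35 participants per group is the standard expectation for feasibility studies" and "We thus aim to recruit 105 participants in total across the three trial arms". That section justifies 35 by the wish to estimate the outcome SD and mentions no allowance for dropout. Of the feasibility data, the Acceptability section says: "These data will help to develop realistic estimates of enrollment accrual and attrition rates". No expected rate is given.

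In a separate sentence, Planned statistical analysis provides for within-group Cohen's d from baseline to each follow-up. Objectives of the trial uses those effect sizes to size a later RCT. The outcome data are labelled preliminary.

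**The concern.** The classical repeated-measures ANOVA needs a complete row of scores. A student seen at baseline and 8 weeks but not at about five months adds nothing to it, even to the baseline-to-8-week contrast. Follow-up is remote self-report over five months and attrition is something the study means to estimate, so some incomplete rows are foreseeable.

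The analysis is meant to supply parameters for the design of a future RCT, from only 35 students per programme. Discarding scores already collected costs precision where there is little to spare. If the chance of answering depends on how a student is doing, the students left in may also show a different average change from all who started. This objection is to the method the article names, not to detail left to another document.

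**Working it through.** **The plan's own figure.** 3 programmes × 35 = 105, which reproduces. The article states no alpha, power, effect size or dropout rate, so there is no power calculation to check.

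**Closed-form precision, n = 35, change SD set to 1.** The 95% half-width is t(0.975, n−1)/√n. With all 35 it is 0.34 SD. The part due to listwise deletion at 8 weeks, compared with using every baseline/8-week pair, is √(n seen at 8 weeks / n complete). The missing rates are assumptions.

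| Missing at 8 weeks / by 3-month follow-up | Seen at 8 weeks | Complete cases | Complete-case half-width (SD) | Listwise factor at 8 weeks |
|---|---|---|---|---|
| 20% / 30% | 28.0 | 24.5 | 0.42 | √(28/24.5) = 1.07 |
| 30% / 50% | 24.5 | 17.5 | 0.51 | √(24.5/17.5) = 1.18 |
| 40% / 60% | 21.0 | 14.0 | 0.58 | √(21/14) = 1.23 |

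Much of the rise from 0.34 comes from the missing data themselves. Only the last column is due to the method.

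**Simulation inputs, all assumed.** n = 35; means 11, 8 and 7.5 at the three visits (true changes 3.0 and 3.5); SDs 4.5, 4.8 and 4.8; correlations 0.5 (baseline–8 weeks), 0.45 (baseline–later) and 0.65 (8 weeks–later). Dropout is monotone and logistic on the previous score, worse scores being likelier to leave. Complete cases are compared with maximum likelihood on all observed scores.

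**Standard error at 8 weeks.**
- At 80%/70% retention (seen at 8 weeks / at both), the complete-case SE is about 5–9% larger than likelihood.
- At 69%/47% it is about 16–25% larger. For example, with log-odds slopes of 0.5 then 1.0 per SD, 1.14/0.93 = 1.23.
- At the later follow-up the difference is small. On a unit-SD scale at 30%/50% missing, likelihood gives 0.23–0.26 and complete cases 0.24–0.25.

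**Bias at 8 weeks, 69%/47% retention, true change 3.00.**

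| Slope before 8 weeks / after 8 weeks | Complete-case change | Relative to 3.00 |
|---|---|---|
| 0 / 0 (completely random) | 3.00 | 0% |
| 0.5 / 0.5 | 3.09 | +3% |
| 0.5 / 1.0 | 3.37 | +12% |
| 1.0 / 1.0 | 3.18 | +6% |
| 1.0 / 0.5 | 2.86 | −5% |
| 1.0 / 0.2 | 2.63 | −12% |

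The two selections pull in opposite directions. Losing high baseline scores shrinks the apparent change, and losing poor 8-week scores inflates it. The net sign depends on which is stronger. These settings illustrate the range and do not bound it: other assumed mechanisms took the 8-week estimate as high as 3.59. At the later follow-up, complete cases gave about 3.0 to 3.4 against 3.5.

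Likelihood on all data stayed at 2.98–3.01 for the 8-week change in every setting. All of these settings are missing at random, so this does not show protection when dropout depends on unobserved scores.

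**Cohen's d on available pairs.** Each d needs only baseline and one follow-up, so it escapes listwise deletion. Under score-dependent dropout the available-pair 8-week change was still 2.44–2.79 against 3.00. With slopes 0.5/1.0 at 69%/47% retention, the ANOVA would show 3.37 and the pairs 2.68: two answers for one programme, from different students.

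**The case against.** The strongest reply is that the ANOVA is not the stated source of the effect sizes for the future trial. Cohen's d is, and it is planned separately. That stands. A reader might infer that the 8-week change used for planning comes only from students who also answered at five months, but the article does not say so. The reply does not rescue the plan, since available-pair d has its own bias under score-dependent dropout.

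Second, bias is not established. A reader might take the ANOVA to inflate the 8-week change by some 13%. That figure belongs to one assumed pair of dropout slopes, and other plausible pairs reverse the sign. Likewise, a claim that the ANOVA needs about 45% more participants mostly restates an assumed retention (0.69/0.47 = 1.47).

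Third, leaving the intervention is not the same as missing an assessment. Objectives of the trial notes "The interview sample will include participants who dropped out of the intervention", but assessments run from first log-in and not from module completion, so a student who stops the modules can still supply scores. It cannot be asserted that the retained cases are the engaged ones.

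Fourth, the article does not say that incomplete cases are deleted. Imputation could be specified in a document not shown, and its absence here is no fault. The point is therefore conditional on the ANOVA being run in its usual form.

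**Conclusion.** The point holds in a limited form. The named method, run classically, gives up 8-week information that a likelihood model would keep. The cost is about 5–9% in the 8-week standard error at 80%/70% retention and about 16–25% at 69%/47%, with little or modest gain at the later visit. Bias is possible in either direction if dropout depends on observed scores, and absent if dropout is completely random. These sizes rest on assumed retention, dropout slopes, means, SDs and correlations, because the article gives no attrition rate. Severity is low to moderate: outcomes are to be interpreted with caution, no decision rule hangs on the ANOVA, and the main aim is feasibility and acceptability.

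**What to change.** Replace the ANOVA with a linear mixed model for repeated measures, fitted per programme: time as a categorical fixed effect, unstructured covariance over the three visits, REML, and all eligible participants with a baseline score. Take from this one model the mean changes, confidence intervals and SDs that feed Cohen's d and the sample-size planning, so that both rest on the same students. Report the number assessed at each visit. Keep the complete-case ANOVA as a sensitivity analysis.

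The cost is a change of wording in the analysis plan and no extra data. The Trial status section puts recruitment at 63 of the planned 105 and ongoing.

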### Eligibility criteria

All registered students at the University of Minnesota will be potentially eligible to participate. Eligibility criteria include being at least 18 years of age and self-reporting mild to severe symptoms of depression (5–27+) on the Patient Health Questionnaire-9 (PHQ-9; [26, 50]), mild to severe symptoms of anxiety (5–21+) on the Generalized Anxiety Disorder (GAD-7; [49]), or mild to severe symptoms of stress (15–34+) on the stress subscale of the Depression, Anxiety and Stress scale-21 (DASS-21; [28]). Students who score below the cutoff score on a given measure may still use the program module related to that measure, although their data will not be included in the analyses. Participants attending face-to-face individual or group counseling will be excluded. This includes all types of psychological therapy such as CBT. At baseline and 3 month assessments, participants will be asked if they have accessed any other form of psychological intervention throughout the time frame of the trial.

Students who score in the “red zone” in terms of risk of self-harm on the screening questions routinely used at SCS (i.e., the Behavioral Health Measure; [6]) will not be referred to the study. Students who score greater than 0 on the PHQ-9 self-harm item in the online screening will be automatically alerted that a counselor will try to reach them. They will be recommended to seek help from BMHC or UCCS. They will be telephoned within 1 working day and contacted by email if they cannot be reached by phone. There is also a “Help” button available on the site which can be accessed at any time and which directs students to a list of counseling resources and health services on campus.

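### The 50% score reduction is named recovery but measures response: on PHQ-9 and GAD-7 it can count students who still score inside the trial's own entry range, and a second, different recovered count stands beside it

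*Protocol article*

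**What the plan says.** The Planned statistical analysis section of the protocol article defines the recovery estimate in one sentence: "An estimation of recovery will be made by identifying the number of participants completing each program who demonstrated a reduction of 50" %, the reduction being taken "from pre-treatment PHQ-9, GAD-7, and DASS-21 stress subscale scores". It sets no condition on where the score ends. The sentence after it adds a second count: "In addition, we will calculate the number of reliably changed and recovered participants using Jacobson and Truax’s [20] criteria".

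The Eligibility criteria section sets the entry ranges. It admits students with "mild to severe symptoms of depression (5–27+) on the Patient Health Questionnaire-9" and those with "mild to severe symptoms of anxiety (5–21+) on the Generalized Anxiety Disorder" scale. For stress it gives 15 to 34+ on the DASS-21 subscale, whereas the Symptom outcome measures section gives that subscale a range of 0 to 21.

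The analysis section also says that outcome results are preliminary and to be read with caution.

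**The concern.** A fall of half the baseline score describes relative change. Recovery describes an end state. The higher the baseline, the higher the score that still satisfies the 50% rule. A PHQ-9 change from 20 to 10, or a GAD-7 change from 18 to 9, counts as recovered, yet that student would meet the symptom criterion for entry again.

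The trial is meant to show proof of concept. A reader who sees a recovery percentage will take it to mean that those students are no longer symptomatic. The planned Jacobson-Truax count will also be reported as recovered. The same student can be recovered in one table and not in the other, and the two percentages cannot be read as estimates of one thing.

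**Working it through.** The protocol states no expected recovery rate, so there is no figure to reproduce. The check has an exact part and an illustrative part.

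**Exact part.** Inputs: PHQ-9 eligible scores 5–27 (23 values) and GAD-7 eligible scores 5–21 (17 values), from the Eligibility criteria section. For baseline b and follow-up f, the 50% rule is met when f ≤ b/2. The student is still in the entry range when f ≥ 5. Both can hold only if b/2 ≥ 5, that is b ≥ 10.

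- PHQ-9: b = 10 to 27, so 27 − 10 + 1 = 18 of 23 eligible scores. The highest end score that still counts is 13 (27 to 13).
- GAD-7: b = 10 to 21, so 21 − 10 + 1 = 12 of 17. The highest end score is 10 (20 or 21 to 10).
- Reverse error: f < 5 with f > b/2 is possible for b = 5, 6 and 7 (for example 7 to 4). These students leave the entry range and are not counted.
- DASS-21 stress on the stated 0–21 range: half of 21 is 10.5, below the entry cut-off of 15, so the overlap cannot occur. On an assumed doubled 0–42 scale with even scores, it starts at 32 (32 to 16) and covers 6 of 14 eligible scores. Baselines 16 to 26 can drop below the cut-off without halving.

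**Illustrative part.** The protocol gives no baseline mean, SD, correlation or expected change, so all of these are assumptions: bivariate normal scores, SD 5, baseline to follow-up correlation 0.5, rounded and clipped to the scale, kept if baseline is 5 or more, 400,000 draws per scenario. Results for PHQ-9:

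| Mean before entry cut-off | Improvement (SD) | Meets 50% rule | Ends below 5 | Meets rule, still ≥ 5 | Below 5, not halved | Share of responders still ≥ 5 |
|---|---|---|---|---|---|---|
| 8 | 0.5 | 38.5% | 33.5% | 8.4% | 3.4% | 22% |
| 8 | 0.8 | 52.1% | 45.7% | 9.8% | 3.4% | 19% |
| 8 | 1.2 | 69.7% | 62.4% | 10.1% | 2.8% | 14% |
| 12 | 0.5 | 22.6% | 13.5% | 10.3% | 1.2% | 45% |
| 12 | 0.8 | 34.3% | 21.5% | 14.2% | 1.4% | 41% |
| 12 | 1.2 | 52.3% | 35.4% | 18.3% | 1.4% | 35% |
| 16 | 0.5 | 11.3% | 3.3% | 8.2% | 0.2% | 73% |
| 16 | 0.8 | 19.1% | 6.3% | 13.2% | 0.3% | 69% |
| 16 | 1.2 | 34.3% | 13.1% | 21.5% | 0.4% | 63% |

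The net excess is the fifth column minus the sixth. At mean 12 and 0.8 SD it is 14.2 − 1.4 = 12.8 points, which equals 34.3 − 21.5. In a program group of 35, that is 0.128 × 35 ≈ 4.5 students. At mean 8 and 0.8 SD it is 9.8 − 3.4 = 6.4 points. GAD-7 under the same assumptions is close: shares of 14–22%, 35–45% and 61–71% at the three means.

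For stress on the doubled scale (SD 8), the rule mostly counts fewer students than the entry cut-off would. At 0.8 SD the figures are 33% against 48% at mean 20, 19% against 25% at mean 26, and 9% against 9% at mean 32.

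**The case against.** The strongest reply is that this is only a label. An end-state count by the Jacobson-Truax criteria is already planned, each count has its own definition and citation, and the outcomes are declared preliminary in a trial whose stated aim is acceptability and feasibility. The score of 5 is an eligibility floor, and nowhere does the protocol say that recovery means falling below it. Counting admissible baselines shows what is possible, not how many students are affected, and the percentages depend on assumed distributions.

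Much of this stands. The entry cut-off is used here as the only symptom threshold that the protocol supplies, not as its definition of recovery. The size cannot be fixed from the documents, and it is modest if most entrants are mild.

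It does not remove the point. Caution about preliminary results deals with imprecision, not with a quantity under the wrong name. The planned Jacobson-Truax count makes the naming problem sharper, because two recovered figures will be published side by side.

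**Conclusion.** The point holds for PHQ-9 and GAD-7, as a matter of definition and reporting. The exact part needs no assumptions: from a baseline of 10, a student can be called recovered while still in the entry range. In every PHQ-9 and GAD-7 scenario tried, the 50% count exceeded the share ending below 5. The PHQ-9 excess ran from 5.0 points (38.5 − 33.5; mean 8, 0.5 SD) to 21.2 points (34.3 − 13.1; mean 16, 1.2 SD), on the assumptions above.

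Four stronger readings are tempting and are not supported:

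- **That recovery is overstated in all three programs.** For stress the overlap is impossible on the stated scale range, and on a doubled scale the comparison often reverses. The entry range and the scale range must be reconciled before anything is said about that measure.
- **That every more severe student who meets the rule is still symptomatic.** Larger falls take some below 5.
- **That the error grows steadily with severity.** The share among responders rises with the baseline mean. As a fraction of all PHQ-9 students analysed at 0.8 SD it is 9.8%, 14.2% and 13.2% at means 8, 12 and 16.
- **That the future trial's sample size would be wrong.** The Objectives and Sample size sections base that on within-group effect sizes and standard deviations, not on a recovery proportion.

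**What to change.** In the planned analysis, call the 50% reduction response. Reserve recovery for the Jacobson-Truax recovered category already planned. Optionally, also tabulate the number of PHQ-9 and GAD-7 end scores below the entry cut-off of 5. Report response and recovery as separate proportions for each program. For DASS-21 stress, first bring the entry range and the scale range onto one metric.

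The cost is a change of wording and, if the optional count is added, one further tabulation from scores already collected. The figure reported as recovery for PHQ-9 and GAD-7 will probably be lower.

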### Symptom outcome measures

The PHQ-9 [26, 50] is a 9-item self-report measure of depression that has been widely used in screening, primary care, and research. The PHQ-9 items reflect the diagnostic criteria for depression outlined in the *Diagnostic and Statistical Manual of Mental Disorders, Fourth Edition–Text Revision* (DSM–IV–TR) [3]. Items are rated on a 0 to 3 scale. Summed scores range from 0 to 27; higher scores reflect a greater severity of depressive symptoms [26, 50].

The GAD-7 [49] comprises 7 items measuring symptoms and severity of GAD based on the DSM-IV diagnostic criteria for GAD. The GAD-7 has good internal consistency (.89) and good convergent validity with other anxiety scales. Items are rated on a 0 to 3 scale. Summed scores range from 0 to 21; higher scores indicate greater severity of symptoms [49].

Stress subscale of Depression, Anxiety and Stress scale-21 (DASS-21). The DASS-21 [28] is an abbreviated version of the original 42-item DASS. It is composed of three 7-item subscales measuring symptoms of depression, anxiety, and stress. Participants will be asked to rate the degree to which they endorse each of the seven stress items on a 4-point scale (0 to 3). Summed scores range from 0 to 21; higher scores indicate greater severity of symptoms. Scores on the DASS-21 have been found to be valid measures of depression, anxiety, and stress in non-clinical samples [17].

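### The 50 % recovery count is confined to programme completers with no stated denominator, and at the mildest GAD-7 baselines a halved score may be less than reliable change

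*Protocol article*

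**What the plan says.** Under Planned statistical analysis, the protocol article estimates recovery by "identifying the number of participants completing each program who demonstrated a reduction of" 50 % in the PHQ-9, GAD-7 or DASS-21 stress score, measured from its pre-treatment value. It gives no denominator, no minimum change in points and no end-state score. The next sentence adds a separate count: "we will calculate the number of reliably changed and recovered participants using Jacobson and" Truax's criteria. That sentence is not limited to completers.

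Three other sections bear on this:

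- **Measures** schedules the three symptom scales at 8 weeks from first login or activation and again 3 months later, whether or not the programme was finished.
- **Eligibility criteria** admits students from the mild range upward: "mild to severe symptoms of depression (5–27" and above on the PHQ-9, "mild to severe symptoms of anxiety (5–21" and above on the GAD-7, and "mild to severe symptoms of stress (15–34" and above on DASS-21 stress.
- **Symptom outcome measures** gives one reliability coefficient only: "The GAD-7 has good internal consistency (.89").

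**The concern.** Completing a self-paced programme happens after baseline and is itself one of the study's adherence outcomes. Students who finish may differ from those who stop in how much they improve. A count confined to finishers leaves out outcome data that the study plans to collect from everyone else. It describes students who complete, whereas the sections on internet-delivered CBT and the Discussion place the trial's value in showing what happens when the programmes are used within existing student services. For that purpose the relevant group is the students who start.

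The second issue is the word recovery. In adjacent sentences it is attached to two different criteria: a relative fall of 50 %, and the Jacobson–Truax classification, which allows for measurement error. For a student who enters with a low score, halving that score can be a very small change in points.

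**Working it through.** **1. Which students are counted**

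The article states no completion, response or recovery rate, so it has no figure of its own to reproduce. Let c be the share of starters who complete, pC the 50 %-response share in completers, and pN that share in non-completers.

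- All starters: R = c × pC + (1 − c) × pN
- Completers over completers: pC, which differs from R by (1 − c) × (pC − pN)
- Completers who respond, over all starters: c × pC, which falls short of R by (1 − c) × pN

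Assumed values: c = 40–60 %, pC = 50 %, pN = 10–20 %.

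| c | pN | Over completers | Completers over all starters | All starters, R |
|---|---|---|---|---|
| 40 % | 10 % | 50 % | 20 % | 0.20 + 0.6 × 0.10 = 26 % |
| 40 % | 20 % | 50 % | 20 % | 0.20 + 0.6 × 0.20 = 32 % |
| 60 % | 10 % | 50 % | 30 % | 0.30 + 0.4 × 0.10 = 34 % |
| 60 % | 20 % | 50 % | 30 % | 0.30 + 0.4 × 0.20 = 38 % |

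The first reading is 12–24 percentage points above R and the second is 4–12 points below it. There are two boundary cases. If pN = pC, the completer rate equals R. If pN = 0, completers over all starters equals R. Between those cases neither reading gives R.

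At the planned 35 per programme and c = 40 %, there are 14 completers and 7 responders among them. The same 7 students can be reported as 7/14 = 50 % or 7/35 = 20 %. The outcomes of the other 21 students enter neither numerator.

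**2. Size of a 50 % fall against reliable change**

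The Jacobson–Truax threshold is RC = 1.96 × SD × √(2 × (1 − r)). Scores are whole numbers, so the smallest fall that meets the rule is half the baseline, rounded up.

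*GAD-7* (r = .89 from the article, SD assumed). RC = 1.96 × √0.22 × SD = 0.92 × SD. A baseline of 5 or 6 needs a fall of 3; a baseline of 7 or 8 needs 4. A 3-point fall is below RC once the SD exceeds 3 / 0.919 = 3.26.

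| SD | RC | Baselines where the smallest 50 % fall is below RC |
|---|---|---|
| 3 | 2.8 | none |
| 4 | 3.7 | 5–6 |
| 5 | 4.6 | 5–8 |

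*PHQ-9* (r and SD both assumed). At r = .85, RC is 3.2 at SD 3 and 5.4 at SD 5, affecting baselines 5–6 and 5–10. At r = .89 and SD 3, RC is 2.8 and no baseline is affected.

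*DASS-21 stress.* From the stated entry score of 15, the smallest 50 % fall is 8 points. Over assumed r = .80–.90 and SD = 2–5, the largest RC is 1.96 × 5 × √0.40 = 6.2. The point therefore does not apply as written. The entry band reaches 34, however, while seven items scored 0 to 3 ("Participants will be asked to rate the degree to which they endorse each of the seven stress items on a 4-point scale (0 to 3") cannot exceed 21, so those two sections need to be reconciled. If the 15 were on a doubled scale, raw entry would start at 8 with a smallest fall of 4, and the point could apply (r = .85 and SD 4 give RC = 4.3).

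**The case against.** The strongest reply is that the plan promises a number and not a rate, and that readers could see the context. The Acceptability section commits to reporting how many students used the programme and to estimating attrition, and module completion is also reported. The wording about completing a programme might loosely mean taking it. Measurement error is covered by the Jacobson–Truax count in the next sentence. Outcome results are described as provisional. The Objectives tie the future sample size to within-group effect sizes and do not mention this count.

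Much of this stands. A reader might infer that the recovery rate is bound to be inflated; the text does not support that. No denominator is stated, and over all starters the same count errs downward if any non-completer responds. A reader might also infer that the plan ignores measurement error, or that halving a score is generally within it. Neither follows: a separate reliable-change count is planned, the GAD-7 result depends on an SD the article does not give, the PHQ-9 result also needs an assumed reliability, and the DASS-21 result fails as written.

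What the reply does not remove is the literal restriction to completers. It sets aside scheduled outcomes whichever denominator is used, and reporting completion levels does not recover the responses of non-completers. If the wording was meant loosely, it still needs correcting. The separate Jacobson–Truax count does not change what the 50 % count is called.

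**Conclusion.** The concern holds in a limited form. As written, the 50 % count rests on a group selected after baseline. On neither denominator does it give the response rate among students who started, except in the two boundary cases shown. Under the assumed completion and response shares, one set of results could be reported as 50 % or as 20–30 %, when the rate among starters is 26–38 %. Those shares are illustrative and none comes from the article.

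Calling the criterion recovery is not justified for the mildest GAD-7 entrants if the SD is above about 3.3. It may not be justified for mild PHQ-9 entrants. It is not shown to be a problem for DASS-21 stress at the stated cut-off and range.

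This should be fixed, but it does not threaten the trial. The study is an uncontrolled feasibility trial, the count is descriptive, and no decision rule is attached to it.

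**What to change.** Under Planned statistical analysis:

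- Compute the 50 % rate, per programme, among all participants who started it and met its cut-off. Use the observed 8-week and 3-month scores of non-completers.
- Add a sensitivity analysis that counts missing follow-up as not improved.
- Report the completer rate as supplementary, labelled as such, with its denominator.
- Call the 50 % criterion response, and reserve recovered for the Jacobson–Truax classification already planned.

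The cost is a change of wording and a little more analysis, with no new data collection. The headline rate will probably be less favourable than a completer rate. Recruitment was still open at 63 participants according to Trial status, so when the article was written the change could be made before analysis.
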